## Abstract

**Background:**

Managing demand for services is a problem in many areas of healthcare, including specialist medical outpatient clinics. Some of these clinics have long waiting lists with variation in access for referred people. A model of triage and appointment allocation has been developed and tested that has reduced waiting times by about a third in community outpatient services. This study aims to determine whether the model can be applied in the setting of a specialist medical outpatient clinic to reduce wait time from referral to first appointment.

**Methods:**

A pre-post study will collect data before and after implementing the Specific Timely Appointments for Triage (STAT) model of access and triage. The study will incorporate a pre-implementation period of 12 months, an implementation period of up to 6 months and a post STAT-implementation period of 6 months. The setting will be the epilepsy clinic at a metropolitan health service in Melbourne. Included will be all people referred to the clinic, or currently waiting, during the allocated periods of data collection (total sample estimated *n* = 975). Data routinely collected by the health service and qualitative data from staff will be analysed to determine the effects of introducing the STAT model. The primary outcome will be wait time, measured by number of patients on the wait list at monthly time points and the mean number of days waited from referral to first appointment. Secondary outcomes will include patient outcomes, such as admission to hospital while waiting, and service outcomes, including rate of discharge. Analysis of the primary outcome will include interrupted time series analysis and simple comparisons of the pre and post-implementation periods. Process evaluation will include investigation of the fidelity of the intervention, adaptations required and qualitative analysis of the experiences of clinic staff.

**Discussion:**

Prompt access to service and optimum patient flow is important for patients and service providers. Testing the STAT model in a specialist medical outpatient clinic will add to the evidence informing service providers and policy makers about how the active management of supply and demand in health care can influence wait times. The results from this study may be applicable to other specialist medical outpatient clinics, potentially improving access to care for many people.

## Background

Waiting for healthcare services is a problem across the care continuum [1] in emergency departments [2], acute hospitals [3] and in ambulatory, community and outpatient settings [4]. Much work has been done on patient flow particularly in the acute setting [5] but there has been increased attention focusing on access, triage and patient flow in non-bed-based services [6–8]. As chronic disease management relies on responsive outpatient services, demand and wait lists for these services has increased [8]. Specialist medical outpatient clinics can have very long wait lists, sometimes up to several years, and some lower priority patients may never receive an appointment [8]. These long waiting times have implications for patient safety with potential risk of deterioration, anxiety and avoidable attendances to the emergency department [8–11]. Waiting for anything within health services is considered to contribute to wastage and avoidable costs [12]. Given the scale and implications of delays in outpatient care, timely and equitable access to specialist medical outpatient clinics is a current government priority [13]. Growing demand and waitlists can appear overwhelming, but the problem should not be seen as intractable [14]. In fact it is a common observation in health services that many waiting lists are relatively stable over time, indicating that supply and demand are actually well balanced, but an entrenched backlog of waiting patients leads to constant delays in care [7, 15].

An innovative model of access and triage, which challenges assumptions about supply and demand, has been developed and evaluated in the community outpatient setting [6, 16, 17]. This setting refers to services provided external to the hospital and includes ambulatory care, community health, and community-based outpatient services. The model, called STAT (Specific Timely Appointments for Triage) [6] is based on data modelling that calculates how many new appointments per week are required to keep up with demand. It also requires a system which maintains patient flow is embedded into practice so that the service actively keeps up with referrals by protecting appointments for new patients in clinician schedules. When commencing the STAT model, a short term, one-off, targeted intervention is implemented that aims to eliminate or markedly reduce the wait list. Each patient referred can then be offered the next available appointment without being prioritised for urgency, as they will *all* be seen in a timely manner. Priority decisions are made at the initial appointment by the treating clinician regarding follow-up or review appointments. Maintaining a constant flow of new patients into the service creates a driver to maximise efficiency across all aspects of patient flow; for example, by modifying practices related to review appointments, discharges and other clinical and administrative processes.

The STAT model showed success in two pilot trials [16, 17] and was then tested in a stepped wedge cluster randomised controlled trial involving eight diverse community outpatient services (including continence clinics, paediatric and adult community health services, community rehabilitation and physiotherapy outpatient clinics) and over 3000 patients [6]. A 34% reduction in waiting time was attributable to the intervention, which was found to be cost effective, sustained at 12 months and well received by staff [18]. It is not known whether the model could be applied to reduce wait times in specialist medical outpatient clinics.

There are similarities between community outpatient services and specialist medical outpatient clinics in that both are attended by community-dwelling people for assessment who are often scheduled for review appointments. They rarely deal with time critical events, with resulting acceptance of waitlists as a way of managing demand. Both service types play an important role in assisting people to manage non-infectious chronic diseases. The efficient management of non-bed-based services impacts on the demand for acute medical care and patient flow throughout the healthcare continuum [19].

There are also some differences between specialist medical outpatient clinics and the community outpatient services in which the STAT model has been trialed to date. Specialist medical outpatient clinics are often medical-only, single-discipline clinics, and are part of the hospital system, along with emergency department and inpatients [19]. In Australia, the funding streams, and reporting, data and governance requirements are quite different, which impacts on the administration of the two service types. The scale of the problem is much larger in specialist medical outpatient clinics where some people have been waiting years for an appointment and the number waiting is significantly greater than the community outpatient services that participated in previous trials.

Delayed access to specialist medical outpatient clinics is a serious problem [20]. This project aims to determine whether an evidence-based model of access, STAT, that reduced waiting time in community outpatient services [6] can be successfully applied to a specialist medical outpatient clinic serving patients with epilepsy to achieve reduced wait time. The specific research questions are: [i] Does the STAT model reduce the average wait time for people referred to a medical specialist epilepsy clinic? [ii] Does the STAT model have an impact on patient and service outcomes? [iii] What can be learned about the process of implementing STAT in this setting?

## Methods

### Design and setting

This is a pre-post study with process evaluation. Routine service data will be collected for a 12-month period prior to the intervention (retrospective data) and for 6 months after the intervention (prospective data). A six-month period is planned for implementation, but the post-implementation period will commence sooner if the existing waiting list has been reduced to below a target threshold (Fig. 1).

**Fig. 1 Fig1:**

Data collection timeline. *Number of people on the waiting list to be collected monthly throughout implementation period and post intervention period (including at the conclusion of the final month), and as available during the pre-intervention period with some missing data anticipated. Average waiting time per month is expected to be available for all time points

A process evaluation will be completed towards the end of the post-implementation phase. It will be based on Medical Research Council’s guidance and framework, combining qualitative and quantitative data to provide information on context, implementation and mechanism of impact [21].

The setting is a first-seizure and general epilepsy clinic at a public metropolitan hospital, referred to as the ‘Epilepsy Clinic’. This specialist medical outpatient clinic runs for one afternoon each week and is staffed by four neurologists. People are referred to this clinic if they have had a first suspected seizure or have previously been diagnosed with epilepsy and require neurologist care. The clinic is funded by Medicare, the Australian universal healthcare system, with no out-of-pocket expense incurred by patients. Upon receipt of a referral, a neurologist triages and allocates each referral a priority code of 1 to 4, with 1 being the most urgent. In general, priority 1 and 2 patients are seen as per government guidelines, within 1 week and 1 month, respectively. However, those triaged as less urgent, priority 3 and 4 are placed on a waitlist and may wait for several years. Over the last 2 years there have been between 600 and 700 people waiting for appointments at any given time, suggesting that supply has been keeping up with demand, but no progress has been made into reducing the entrenched backlog of waiting patients or getting to the lowest priority patients. The longest waiters have been on the waiting list for over 7 years.

### Participants

The participants are people who have been referred to the epilepsy clinic and who received their first appointment during the 12 month period prior to implementation (pre-intervention cohort) or during the 6 months following implementation of the STAT model (post-implementation cohort). In addition, the number of patients on the waiting list (referred but not allocated an appointment) will be tracked monthly from the beginning of the implementation period to the end of the post-implementation period.

Clinic staff, including neurologists, administrative staff and management, will be invited to participate in a focus group where data will be collected for evaluation of process.

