Step 4 involves setting up or modifying the neurologists’ booking diaries to match the demand calculation. For example, if the final calculation indicated that 12 new appointments would be required each week to meet average demand, then the 4 neurologists would need an average of 3 new appointment slots available in each weekly clinic.

Step 5 sees a change in process where people referred are booked straight into an appointment without being placed on a waitlist. *All* referrals will be seen promptly and triage decisions regarding priority of ongoing management will be made at the first appointment by the consulting neurologist. Making these changes will likely have a flow-on effect and adjustments to caseload management are anticipated. For example, absorbing a constant flow of new assessments may instigate a review of discharge practices and management of review appointments.

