### Outcome measures

Service and patient data will be collected for all people admitted during the trial period from health service databases.

The primary outcome measure will be wait time, measured by (i) the mean number of days waited from referral to first appointment for patients seen across the entirety of the pre and post intervention periods and for each month of the trial and (ii) the number of patients on the wait list at monthly time points.

Secondary outcomes will be service measures, patient outcomes and qualitative data to evaluate staff perceptions (Table 1). Service measures will be rate of failure to attend, rate of discharge, and appointment outcome (attended and scheduled for review; attended and discharged; or failed to attend). In addition, the waiting time of the longest waiters (90th percentile and mean of top 3 waiters) will be collected monthly from the beginning of the implementation and throughout the post-implementation phase. Outcomes from the initial waitlist reduction strategy will be recorded as well as costs associated with implementation. The number of new referrals received will be tracked monthly to monitor changes in demand and provide context for interpretation of results.

**Table 1 Tab1:** Outcome measures and collection phase

	Pre	During	Post
Primary outcome			
Wait time			
Number of patients on the wait list	✓	✓	✓
Number of days waiting from referral to first appointment	✓		✓
Secondary outcomes			
Service measures			
Number of appointments delivered (new and review)	✓		✓
Outcome (booked for review, failed to attend, discharged)	✓		✓
Wait time to next first appointment and next review appointment		✓	✓
Number of days waited by the longest waiters (90th percentile and top 3)	✓	✓	✓
Outcomes from initial waitlist reduction strategy (booked for assessment or removed from waitlist)		✓	
Cost directly associated with implementation		✓	
Patient outcomes			
Hospital admissions (number and total days)	✓		✓
Emergency department presentations between referral and first appointment	✓		✓
Change in management or risk between referral and first appointment	✓		✓
Staff perception			
Staff focus group			✓

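### The monthly wait-list count, measure (ii) of the primary outcome, leaves out anyone already given a date, so STAT lowers it partly by relabelling patients who are still waiting

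*Protocol article*

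**What the plan says.** Under Outcome measures there is one primary outcome, wait time, measured in two ways: (i) "the mean number of days waited from referral to first appointment for patients seen", and (ii) "the number of patients on the wait list at monthly time points". The list behind (ii) is defined in Participants: "the number of patients on the waiting list (referred but not allocated an appointment) will be tracked monthly". Data analysis puts both monthly series through interrupted time series regression and expects a level change.

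The booking process differs between phases. Before STAT, according to Design and setting, referrals triaged as "priority 3 and 4 are placed on a waitlist and may wait for several years". After STAT, Step 5 (Intervention) means that "people referred are booked straight into an appointment without being placed on a waitlist". Table 1 records the result of the backlog strategy for each patient as either a booked assessment or removal from the list.

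Nothing in the article redefines the count to take in people who have a date but have not been seen.

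**The concern.** A count is comparable across an interruption only if the same kind of patient is counted on both sides. Here a low-priority patient referred before STAT stays in the count for as long as no date is given. An identical patient referred after Step 5 leaves it on booking, whether the date is one week or six months away. The wording of the definition stays the same, but the intervention moves people across its boundary without their being seen.

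What is at stake is the reading of measure (ii). A level change is the hypothesised result, and the change in booking process would contribute to one regardless of any change in the number of people waiting.

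**Working it through.** **The plan's own figure.** The only power figure is for measure (i). Inputs from Data analysis: mean 72 days, SD 85, 40% reduction, 50% less variability, n = 975, two-tailed alpha 0.05. I assume a 650/325 split (12:6 months) and read the reduced variability as a halved SD, 42.5.

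- Difference: 0.40 × 72 = 28.8 days.
- Standard error: √(85²/650 + 42.5²/325) = √(11.12 + 5.56) = 4.08.
- 28.8/4.08 = 7.05, so power exceeds 0.9999. With no fall in SD it is 0.9987.

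The stated power of over 0.99 reproduces. It says nothing about the count, for which no power figure is given.

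**Who is counted under the Participants definition.**

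| Patient not yet seen | Counted? |
|---|---|
| Before STAT, priority 3 or 4, no date given | Yes |
| After Step 5, new referral with a date, near or far | No |
| Backlog patient given a date in Step 3 | No, from the day of booking |
| Backlog patient with no date yet | Yes |

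Rows two and three are the relabelling. Row four is why the count moves towards zero for new referrals without having to reach zero overall.

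**Illustration of the number hidden.** In a steady state, people waiting = referral flow × mean wait (Little's law). The article gives no referral rate. I assume that the 975 patients over 18 months approximate the flow: 975/18 = 54.2 a month, or 54.2/30.44 = 1.78 a day.

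| Mean wait | New referrals not yet seen | Counted under the definition |
|---|---|---|
| 43.2 days (72 less 40%) | 1.78 × 43.2 ≈ 77 | about 0 |
| 72 days (unchanged) | 1.78 × 72 ≈ 128 | about 0 |
| 144 days (doubled) | 1.78 × 144 ≈ 256 | about 0 |

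The middle column scales with the assumed flow: at 20% below or above it, the 72-day row becomes about 103 or 154. The right-hand column does not move.

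**Why these cannot be set against the baseline.** The article reports that "there have been between 600 and 700 people waiting for appointments at any given time". The assumed flow is 975/1.5 = 650 a year, so 600 to 700 waiting would imply a mean wait of 600/650 × 365 = 337 to 700/650 × 365 = 393 days, not 72. The 72 days is a mean among patients seen, and priority 1 and 2 patients are generally seen within a week and a month. It does not describe those still on the list.

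**The case against.** The strongest reply is that the study does not depend on this count. Measure (i) is listed first, carries the power calculation and is unaffected by booking status. The secondary wait to the next first appointment would also show a long booked delay. A reader might infer that an ineffective or harmful intervention would be declared a success. The documents do not support that: nothing lets the count alone settle the result, and the two measures are ways of measuring one primary outcome. This part of the objection stands. It has limits: measure (i) covers only patients seen within the window, so someone booked but unseen at its end appears in neither primary measure, and Table 1 collects the wait to next appointment only during and after implementation.

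Second, Step 5 concerns new referrals. The existing backlog leaves the list only through Step 3, which may include audit, extra clinics or telephone consultations, so much of the fall could be real. That also stands. Table 1 would show how many backlog patients were booked rather than removed, but the monthly series does not make that separation.

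Third, the definition is a parenthesis in Participants, and Outcome measures does not repeat it. It is nevertheless the only definition given, and followed as written it produces the problem.

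**Conclusion.** The point holds, confined to measure (ii). As defined, the monthly count mixes real reduction with relabelling, and its time series cannot tell them apart. This follows from the definition, Step 5 and Table 1 read together, and needs no numerical assumption.

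The size is known only by illustration: roughly 77 to 256 unseen new referrals counted as about 0 for mean waits of 43 to 144 days. That rests on a steady state and on 975/18 months standing in for the referral flow. A reader might set 128 against 600 to 700 and read a fall of about 80% or 100% as the size of the artefact. The inputs do not fit together, so neither percentage is supported. Nor do the documents show that the whole fall would be artefact.

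**What to change.** In Participants and Outcome measures, define the list for all phases as accepted referrals that have not yet attended a first appointment at month end, whether or not a date is booked. Use that series in the interrupted time series regression. Report the unallocated count separately, as a process measure of Step 5.

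The cost is modest but not nil. Referral and first-appointment dates are already needed for measure (i), but the query must also include referrals never seen, with the date each was withdrawn or removed. The Fig. 1 legend already expects gaps in the pre-intervention counts. Rebuilding them from dates may fill some, but some months may not be recoverable. The apparent reduction will be smaller than under the present definition.

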### Data analysis

Primary and secondary data from the pre and post-intervention cohorts will be compared using *t*-tests for continuous data (waiting time, number of appointments, scheduled appointments, missed appointments, emergency department presentation and hospital admission data, and changes in patient risk and/or management) or equivalent non-parametric tests as appropriate. Chi squared statistics will be used to compare nominal patient-level data for the two groups.

The mean number of days waited each month and number of people on the waiting list at sequential time points will be analysed using interrupted time series regression, following methods described by Bernal [23]. It is hypothesized that the intervention will show a 40% reduction in wait time and the impact model will be a level change (Fig. 2).

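### The protocol describes pre-period wait-list counts in three different ways, so the level change for this primary measure rests on an unstated number of baseline months; the longest-waiter measure has a similar conflict

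*Protocol article*

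**What the plan says.** **Wait-list size.** Outcome measures makes this the second part of the primary outcome: "ii) the number of patients on the wait list at monthly time points". Its collection period is given in three places.

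- Participants: the count "will be tracked monthly from the beginning of the implementation period to the end of the post-implementation period".
- Fig. 1 caption: monthly counts through the implementation and post periods, and "as available during the pre-intervention period with some missing data anticipated".
- Table 1: the list-size row is ticked for Pre, During and Post, with no qualification.

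**Longest waiters (secondary).** The Outcome measures text says these values "will be collected monthly from the beginning of the implementation and throughout the post-implementation phase". Table 1, in the same section, ticks Pre, During and Post for the row beginning "Number of days waited by the longest waiters (90th percentile and top 3".

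**Analysis.** Under Data analysis, the "number of people on the waiting list at sequential time points will be analysed using interrupted time series regression", with a level change as the hypothesised impact. Separately, "Primary and secondary data from the pre and post-intervention cohorts will be compared using" t-tests or non-parametric equivalents. The sample size paragraph counts up to 24 monthly observations and expects them to be evenly distributed.

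**The concern.** A level change from the pre-implementation baseline needs a pre-implementation series. For list size, one part of the protocol starts the series at implementation, another promises whatever pre-period counts happen to exist, and a third promises them all. Nowhere is it stated how many of the 12 months are held, or which ones. The precision of the estimate, and its freedom from selective gaps, therefore depend on something the plan leaves open.

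This matters because mean days waited, the other primary measure, is computed on patients who were seen. The clinic's problem as described under Design and setting is a standing backlog of 600 to 700 people, some waiting over 7 years. List size and the longest-waiter values show that backlog most directly, and these are the two measures whose baseline is not secured.

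**Working it through.** **1. The plan's own figure.** The stated power is over 0.99 for a 40% reduction in mean wait.

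- Inputs from the sample size paragraph: mean 72 days, SD 85, n = 975, two-sided alpha 0.05, variability halved after implementation.
- Difference: 0.40 × 72 = 28.8 days.
- The split between periods is not given. I assume 650 pre and 325 post (12 and 6 months at a constant rate).
- With the post SD at 42.5: SE = √(85²/650 + 42.5²/325) = √(11.115 + 5.558) = 4.083. Then 28.8/4.083 − 1.96 = 5.09, and power exceeds 0.9999.
- With SD 85 in both periods: SE = √(11.115 + 22.231) = 5.775. Then 28.8/5.775 − 1.96 = 3.03, and power is 0.9988.

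The figure reproduces. It concerns days waited and does not depend on the disputed series.

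**2. Monthly points for list size.**

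- Table 1: 12 + 6 + 6 = 24.
- Fig. 1 caption: fewer than 24, number not stated.
- Participants text taken alone: 6 + 6 = 12, none of them pre-period. The caption also mentions a reading at the end of the final month, so start-of-month readings plus that one could make 13.

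**3. Effect on the level change.** Assumptions: pre months 1–12, implementation 13–18, post 19–24; independent errors with SD σ; implementation months excluded; missing-month patterns chosen for illustration.

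- Without a trend term: SE/σ = √(1/n_pre + 1/n_post).
- With a common linear trend: SE/σ = √(1/n_pre + 1/n_post + d²/W). Here d is the distance between the mean months of the two segments, and W is the sum of their within-segment sums of squares of month.

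Worked example, all 12 pre months: d = 21.5 − 6.5 = 15 and W = 143 + 17.5 = 160.5. Without trend, √(1/12 + 1/6) = 0.500. With trend, √(0.25 + 225/160.5) = 1.285.

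| Pre months held | SE/σ, no trend | SE/σ, trend |
|---|---|---|
| All 12 | 0.500 | 1.285 |
| 6, alternate months | 0.577 | 1.755 |
| 6, the last six | 0.577 | 2.109 |
| 3 (months 3, 7, 11) | 0.707 | 2.179 |
| 1 (month 12) | 1.080 | 2.515 |
| 0 | not estimable | not estimable |

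Six months against 12: 0.577/0.500 = 1.15 without trend; 1.755/1.285 = 1.37 and 2.109/1.285 = 1.64 with trend.

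**4. Sensitivity to the handling of implementation months.**

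- With their own phase term, the no-trend ratios are unchanged. The trend ratios are 1.619/1.230 = 1.32 and 1.754/1.230 = 1.43.
- Counted as intervention, the no-trend ratio is 0.500/0.408 = 1.22. The trend ratios are 0.992/0.819 = 1.21 and 0.869/0.819 = 1.06.
- With no pre months, both of these models remain not estimable. Only if implementation months are used as the baseline does an estimate exist (0.577 without trend, 1.167 with). That baseline is weak, because Step 3 of the intervention is reducing the list during those months.

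**The case against.** The strongest reply is that the passages on list size can be read together. Participants does not say that counts are taken only from implementation. Design and setting provides for 12 months of retrospective routine data, and the Fig. 1 caption openly describes full prospective counts plus whatever earlier counts exist. The reported range of 600 to 700 over two years shows that some historical counts are held. Handling of missing months can be left to an analysis plan. This largely stands. It rules out saying that list size has no baseline, which a reader might infer from the Participants sentence alone. It does not settle how many pre-period months the level change rests on, and Table 1 still promises more than the caption does.

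For longest waiters, a value at the start of implementation could serve as a starting level, and Data analysis does not name this measure for time series regression. A reader might infer that it needs a baseline segment; the plan sets no such requirement. What remains is the unreconciled conflict between text and table, for a secondary measure that falls within the general pre/post comparison. Nor is it the sole measure touching people who have waited for years: list size includes them, and the reach evaluation and the record of the waitlist reduction strategy also cover them.

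Finally, the gaps the caption anticipates may mean that old lists cannot be fully recovered. That is fair, and complete recovery should not be assumed.

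**Conclusion.** The concern holds as an internal inconsistency with a consequence for one of the two primary measures. The pre-period baseline for list size is incomplete and unassured, not absent. If half the pre months were missing, the standard error of its level change would rise by about 15% without a trend term and by 37% to 64% with one. These figures assume a six-month implementation period left out of the model, independent errors and illustrative missing patterns; other treatments of the implementation months give 6% to 43%. With no pre months the change is not estimable unless implementation months stand in as the baseline.

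The ceiling of 24 observations cannot be relied on for this series when gaps are already expected, and even spacing cannot be assumed. A reader might infer that the whole primary outcome or the stated power is undermined. The documents do not support that: the Fig. 1 caption expects monthly average waiting time at all time points, and the power statement concerns that measure and reproduces.

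**What to change.** 1. Make Participants, Outcome measures, the Fig. 1 caption and Table 1 agree on when list size and the longest-waiter values are collected.
2. Rebuild each pre-period month-end list retrospectively from referral, appointment-allocation (or first-appointment) and removal dates.
3. Use the protocol's definition of the list (people with a referral who have not yet been given an appointment) identically in all phases. This matters because Step 5 books referrals directly. A definition that also counts people booked but not yet seen would diverge from the protocol's, most of all after implementation. If allocation dates are not held, apply one alternative definition to every phase as a stated sensitivity analysis.
4. From these lists compute list size, the 90th percentile and the top-3 mean, taking the longest waiters to be people still on the list.
5. Report how many pre-period months and records could not be rebuilt, and restate the number of monthly observations for the list series accordingly.

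The cost is a modest data query and some text edits. Removal or allocation dates may be imperfect for some old referrals, so recovery of all 12 months is a target and not a certainty.
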